### Sample size and recruitment

We aim to recruit 120 people with MS together with their primary caregivers (therefore, the potential sample is up to 240 subjects; 120 patients and 120 caregivers).

Inclusion criteria for patients with MS will be:Diagnosis of relapsing-remitting or secondary progressive MS (divided into 60 relapsing-remitting and 60 secondary progressive during the recruitment procedure);Ability to communicate and to understand tasks;No change of disease-modifying treatment in the 3 months before the enrolment;No clinical relapses or use of steroid treatment during the 4 weeks before the enrolment;Availability of a personal computer, smartphone, or tablet (compatible with the software);Provided informed consent for study participation;Age >18 years.

Inclusion criteria for caregivers will be:Being a person who lives with the MS patient and provides him or her with the most care and assistance;Ability to communicate and to understand tasks;Availability of a personal computer, smartphone, or tablet (compatible with the software);Provided informed consent for study participation;Age >18 years.

Exclusion criteria (referred to both patients and caregivers) will be:Severe co-morbidity that would reduce life expectancy to less than one year (e.g., end-stage oncological diseases or severe cardiac dysfunction);Severe neuropsychological impairment (e.g., dementia), as indicated by testing below the fifth percentile in at least 3 of 6 dimensions of neuropsychological functioning tests (i.e., attention and concentration, processing speed, executive function, verbal memory, and verbal processing);Psychosis or dissociative disorders;Pregnancy.

Subjects will be recruited at the Multiple Sclerosis Center of the Fondazione Don Gnocchi Hospital, in Milan.

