### Analysis

The general linear model will be used to test interaction effects between treatments (experimental versus control groups) and over time (three repeated measures). Six models will be built, one of each primary outcome measure (quality of life, anxiety, and depression) and separately for patients and caregivers. Type I error inflation due to multiplicity of tests will be controlled by the correction of critical alpha (0.05/6 = 0.008). Violations of the parametric model assumptions will be tested and explored with ad-hoc techniques. If violations are detected, robust methods, data manipulation, or statistical corrections will be applied accordingly. An intention-to-treat analysis approach will be used. Missing data will be imputed with multiple imputation techniques [28]. According to power analysis calculation (G*Power), a total sample size of 110 patients (and caregivers) will allow the detection of small interaction effects (*η*^2^ = 0.01) with a 0.85 statistical power, alpha = 0.05 and an assumed nonsphericity correction (*ε*) of 0.75. Significant interaction effects will be followed by contrast analysis. A similar analysis will be conducted for the actigraphic data, with a reduced sample size, enabling the detection of a small-medium interaction effect under the same conditions.

The mediation effect of the meditation level will be examined by adding a within-subjects factor to the general linear models and the interactions with the treatment effect will be explored according to the guidelines of Kraemer *et al.* [29]. In addition, moderation effects by sex, age, and number of accesses to the software will be examined by adding the relative between-subjects factors into the general linear models and the interactions with the treatment effect will be explored according to the same guidelines [29].

Data analysis will be performed with R and SPSS software.

Data collection and analysis will begin at month 1, and will last 21 months, 1 month after the last follow-up data gathered.

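### The 0.85 power is stated at alpha 0.05, but all six primary tests are made at 0.05/6 = 0.008; at that level the same inputs give about 0.63

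*Protocol article*

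**What the plan says.** Everything on this point stands in one paragraph, under Analysis in the protocol article.

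- **Tests.** The general linear model is to "test interaction effects between treatments (experimental versus control groups) and over time (three repeated measures"). The number of primary tests is fixed: "Six models will be built, one of each primary outcome measure (quality of life, anxiety, and depression) and separately for patients and caregivers".
- **Significance level.** "Type I error inflation due to multiplicity of tests will be controlled by the correction of critical alpha (0.05/6 = 0.008").
- **Power.** The calculation, made in G\*Power, takes "a total sample size of 110 patients (and caregivers") and a small interaction effect (eta-squared 0.01), "with a 0.85 statistical power, alpha = 0.05 and an assumed nonsphericity correction" of 0.75.

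Under Sample size and recruitment, the target is 120 patients with their primary caregivers. No other section restates the power or gives it at 0.008.

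**The concern.** Power belongs to a particular test at a particular significance level. The paragraph commits all six primary tests to 0.008 and then reports power for a test at 0.05 that the trial will not perform. A stricter threshold with the same N and the same effect must lower the power, so 0.85 cannot be the power of any primary test on the inputs that produced it.

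At stake is what the trial can be said to be able to detect. A reader who takes the sentence at face value believes that each primary test would miss the target effect 15% of the time. At the level actually used, the figure is well over twice that. This bears on the sample size justification and on how much a non-significant primary result can tell us.

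**Working it through.** **Inputs from the article.** Groups k = 2; repeated measures m = 3; N = 110 (recruitment target 120); eta-squared = 0.01; epsilon = 0.75; alpha = 0.05 in the power sentence; alpha = 0.05/6 = 0.00833, printed as 0.008, for the tests.

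**Input not in the article.** The correlation rho among the repeated measures. It is treated as unknown and solved for in step 1.

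**Formulas** (noncentral F for the within-between interaction):

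- f² = eta²/(1 − eta²) = 0.01/0.99 = 0.0101
- lambda = f² × N × m × epsilon/(1 − rho)
- df1 = (k − 1)(m − 1) × epsilon = 1 × 2 × 0.75 = 1.5
- df2 = (N − k)(m − 1) × epsilon = 108 × 2 × 0.75 = 162 for N = 110
- Power = the probability that a noncentral F(df1, df2, lambda) exceeds the critical value of the central F at the chosen alpha

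**Step 1: reproduce the stated 0.85 (N = 110, alpha 0.05).** The numerator of lambda is 0.0101 × 110 × 3 × 0.75 = 2.50. Power is 0.769 at rho 0.70, 0.842 at 0.75 and 0.914 at 0.80. It equals 0.85 at rho of about 0.755, where lambda = 10.22. The stated figure is therefore obtainable at its declared alpha, and it implies a rho of about 0.755.

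**Step 2: same lambda, corrected alpha (N = 110).** With lambda held at 10.22:

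- alpha 0.05/6: power 0.637
- alpha 0.008: power 0.631

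**Step 3: does the result depend on the unstated rho?** Hardly, once 0.85 is accepted, because 0.85 at alpha 0.05 fixes lambda directly. Solving for lambda under other numerator degrees of freedom and re-evaluating at 0.05/6 gives 0.632 (df1 = 1), 0.637 (df1 = 1.5) and 0.639 (df1 = 2).

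**Step 4: all 120 couples give full data.** Lambda rises to 10.22 × 120/110 = 11.15 and df2 to 118 × 1.5 = 177. Power is 0.688 at 0.05/6 and 0.683 at 0.008.

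**Step 5: effect detectable with 0.85 power at the corrected alpha (rho 0.755).** For N = 110 the lambda needed is about 15.2 (0.05/6) to 15.3 (0.008). This corresponds to an eta-squared of 0.0148 to 0.0149, so about 0.015. For N = 120 it is 0.0136 to 0.0137, so about 0.014.

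**Size of the gap.** 0.85 − 0.63 = 0.22 at N = 110, and 0.85 − 0.68 = 0.17 with 120 complete couples. The chance of missing the target effect in a given test goes from 0.15 to about 0.37 (N = 110) or 0.32 (N = 120).

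**The case against.** The best defence is that the paragraph hides nothing. It declares alpha = 0.05 openly, and the 0.85 is reproducible at that alpha with a plausible correlation. The planned tests, the multiplicity correction and the sample size would all stay as they are. The article also condenses a fuller protocol, which may hold more detail.

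Most of that is true, but it does not remove the inconsistency. The article itself prints both the corrected threshold and the power at the uncorrected one, so this is a conflict in what it states, not a detail left out.

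The defence does rule out several stronger readings that a reader might infer:

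- **That 0.63 is a ceiling.** It is not. It holds for N = 110 with the 0.85 taken as given. With 120 complete couples the figure is about 0.68 to 0.69. A correlation of 0.80 would give about 0.75 at N = 110, although the power at alpha 0.05 would then be 0.91 and not the stated 0.85.
- **That the missing correlation is itself a defect, or that true power is far lower still.** An article may leave out a software input. Lower correlations give lower power, but nothing in the document points to them, and they would contradict the stated 0.85.
- **That caregivers have still less power because fewer will enrol.** The recruitment section says "therefore, the potential sample is up to 240 subjects; 120 patients and 120 caregivers", which allows for a shortfall but does not predict one. The power sentence already works with 110, ten below target. No caregiver-specific figure can be derived.
- **That null results will be misread.** The document plans no equivalence or futility claim. Over-reading is a risk of leaving the sentence uncorrected, not something the plan proposes.

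**Conclusion.** The power statement is wrong as written: it is given at a significance level that no primary test uses. At the level that is used, power per test for an eta-squared of 0.01 is about 0.63 to 0.64 at N = 110, or about 0.68 to 0.69 if all 120 couples give full data. The effect detectable with 0.85 power is about 0.015 or 0.014 respectively.

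These figures rest on accepting the stated 0.85 at alpha 0.05 and N = 110 (implied correlation about 0.755), on epsilon = 0.75, and on the noncentral F for the interaction. They are powers for one test at a time, not for the set of six. The fault is a mismatch between two sentences. The 0.85 is not shown to be miscalculated at its own alpha, and the Bonferroni correction is not in doubt. Nor do the documents oblige the trial to recruit more participants; what they require is that the stated power match the stated test.

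**What to change.** Keep the sample size and the corrected alpha. Replace the power sentence with one computed at alpha = 0.05/6, using the correlation among repeated measures that the sponsor entered in G\*Power, and state that value. The stated 0.85 implies about 0.755, but this was obtained by working backwards and should not be written in as the sponsor's assumption unless it was.

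If the sponsor's input agrees with the stated 0.85, the sentence could read: at alpha = 0.008 and N = 110, power for each primary test is about 0.63 for an eta-squared of 0.01 and about 0.85 for an eta-squared of 0.015. The figure for 120 complete couples (about 0.68) can be added.

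The change is to wording only. It needs no extra participants and changes no test. The one cost is a less favourable stated power.

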### Screening, assessments, and randomization

Screening will be conducted by doctors of the Multiple Sclerosis Center of the Fondazione Don Gnocchi Hospital, considering the inclusion and exclusion criteria.

Subsequently all subjects will be fully assessed at baseline (T1), after 2 months (T2, corresponding to the end of treatment) and at 6-months follow-up (T3).

Primary outcome measures will assess quality of life, together with depression and anxiety. Attained mindfulness level, quality of sleep, and participation level will be considered secondary outcome measures. Questionnaires will be self-reported, with online assessments (therefore accessible from subjects’ own computers). Subjects will be also assessed, with a qualitative approach (semi-structured interview), about possible side effects or adverse events of the treatment, at T2 and T3, by a psychologist. The interview will be conducted in person or via teleconference call (e.g., Skype).

Subsequently, randomization will be conducted by the principal investigator who will be fully blinded to all patient information, except the study identification numbers of patients. Patient–caregiver couples will be considered as single units for the randomization.

Subjects, consisting of patient–caregiver couples, will be randomly allocated into two groups (60 patients + their caregivers for each groups, with a stratification referred to subjects recruited for the instrumental assessment):Meditation telemedicine intervention, developed and tested.Control group, receiving psycho-education, utilizing a telemedicine approach.

The intervention phase will begin at the end of the pilot study (month 6) and will last 11 months.

In the mainframe of the general study, an objective evaluation of the impact of treatment on sleep disturbance and fatigue will be conducted with an instrumental assessment. During the software development and testing phases, we will consecutively recruit 40 subjects with MS (first recruitment round), with the same inclusion criteria, who report disturbed sleep. Each of these subjects will undergo actigraphy. The sensor will be worn by each subject for two consecutive weeks and will provide objective information about quality of sleep and daily activity, with synthetic data summarized by a computer software.

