### Measures

#### Self-report measures

The Multiple Sclerosis Quality of Life*-*54 questionnaire is a multidimensional health-related quality of life measure that combines both generic and MS-specific items in a single instrument [21]. It is composed of 12 subscales along with two summary scores, and two additional single-item measures. The subscales are: physical function, role limitations, physical, role limitations, emotional, pain, emotional well-being, energy, health perceptions, social function, cognitive function, health distress, overall quality of life, and sexual function. The scale has demonstrated good psychometric properties and has been translated into Italian [22]. This assessment will be completed only by patients.

The Medical Outcomes Study Short*-*Form*-*36 health survey will be used to assess caregivers’ quality of life. This is a 36-item scale constructed to survey health status and quality of life [23], that investigates eight health aspects: limitations in physical activities because of health problems; limitations in social activities because of physical or emotional problems; limitations in usual role activities because of physical health problems; bodily pain; general mental health; limitations in usual role activities because of emotional problems; vitality; general health perceptions. It is one of the most widely used instruments for the evaluation of quality of life in many countries in the world, including Italy [24].

The Hospital Anxiety and Depression Scale will be used to assess depression and anxiety levels of all the subjects. This comprises 14 items rated on a four-point Likert scale [25]. It is designed to screen for the presence and severity of depression and anxiety in patients with a physical symptomatology. The scale mainly includes items that are not related to somatic symptoms of depression.

The Langer Mindfulness Scale will be used to assess the level of meditation attunement. This is a 14-item questionnaire that assesses three domains associated with mindful thinking: novelty seeking, engagement, and novelty producing [26]. An individual who seeks novelty perceives each situation as an opportunity to learn something new. An individual who scores high in engagement is likely to notice more details about his or her specific relationship with the environment.

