## Discussion

Consistent with previous efforts that used new technology platforms to support psychological interventions [17, 18], the aim of this study is to investigate the impact of an MS-specific telemedicine meditation intervention on the quality of life of people with MS and their caregivers. Specifically, the main aim of this study is to create and test a multimedia software package that can teach meditation at home, following the specific requirements of people with MS, in order to improve quality of life and quality of sleep and reduce fatigue of patients with MS and their caregivers. We also aim to gain insight on the efficacy of a telemedicine meditation intervention on a range of important outcomes, giving a greater understanding of the underlying processes of change.

We anticipate some study limitations or threats to the protocol efficacy. The first is related to the virtual nature of the experience. The online platform could be an excessively awkward intermediary, and might reduce the feasibility of the experience compared with meditation in a group. Moreover, the synchronous communication that characterizes video-chat interactions could be slowed down by overlapping in turn-taking, or by delays and problems of internet connections.

Despite possible limits, this study has several key strengths. It consists of a meditation intervention specifically based on MS features and needs, aimed at improving the management of MS symptoms, such as numbness, fatigue, or tingling. The intervention is addressed not only to patients but also to caregivers, who may wish to obtain benefits from a meditation intervention. Moreover, the protocol is designed to reduce participation barriers, either for practical reasons (e.g., work activities) or related to physical disabilities that prevent movement. Finally, the efficacy of the experimental condition is compared with an active intervention (psycho-education group) to provide a reliable estimation of changes promoted by this specific intervention, reducing placebo and Hawthorne effects.

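### The mediation analysis as described rests on a treatment-by-mindfulness interaction, which does not estimate an effect of treatment through mindfulness

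*Protocol article*

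**What the plan says.** The base model is a repeated-measures analysis: "The general linear model will be used to test interaction effects between treatments (experimental versus control groups) and over time (three repeated measures". There are six such models, for three primary outcomes in patients and in caregivers.

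For mediation, the Analysis section says: "The mediation effect of the meditation level will be examined by adding a within-subjects factor to the general linear models". The same sentence continues that "the interactions with the treatment effect will be explored according to the guidelines" of a cited source. The next sentence handles moderation in a parallel way: "moderation effects by sex, age, and number of accesses to the software will be examined by adding the relative between-subjects factors", again with interactions with treatment explored under the same source.

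I take the meditation level to be the mindfulness score, because the section on self-report measures says: "The Langer Mindfulness Scale will be used to assess the level of meditation attunement". That scale is a 14-item questionnaire. The section on screening and assessments says that "all subjects will be fully assessed at baseline (T1), after 2 months (T2, corresponding to the end of treatment" and again at six-month follow-up (T3). The Discussion names, among its hopes for the trial, "giving a greater understanding of the underlying processes of change".

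**The concern.** In the base model the within-subjects factor is time, which has the same three levels for everyone. A mindfulness score is different in kind. It varies between people and over time, and the intervention is intended to move it. It can enter a model as a covariate or as a second response, but not as a design factor.

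The quantity to be examined is also the wrong one for the question. Mediation has two links: arm to mindfulness, and mindfulness to outcome given arm. The text describes neither and names no indirect effect. It names only interactions with treatment, the device it also uses for moderation.

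What is at stake is the trial's account of how the intervention works. A significant interaction could be reported as mediation where there is none, and a real indirect effect could be missed.

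**Working it through.** The article gives no effect size, sample size or power for the mediation analysis, so there is no stated figure to reproduce. The check is whether the described test responds to mediation.

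**Inputs.** N = 110 is the total in the power statement ("a total sample size of 110 patients (and caregivers) will allow the detection of small interaction effects"). The path sizes are not in the document. Those below are illustrative assumptions, in units of the residual SD.

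**Reading 1: mindfulness as a predictor, with its interaction with arm.** With arm T coded −0.5 and +0.5:

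- M = a·T + error
- Y = c·T + b·M + d·T·M + error

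The effect of arm through mindfulness, using the slope in arm t, is a × (b + d·t). The interaction test examines only d. If d = 0 the indirect effect is a·b, which may be large. If a = 0 the indirect effect is zero whatever the value of d.

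Scenario A, full mediation: a = 0.6, b = 0.5, c = 0, d = 0. The indirect effect is 0.6 × 0.5 = 0.30.

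Scenario B, no mediation: a = 0, b = 0.5, c = 0, d = 0.6. The slopes are 0.5 − 0.5 × 0.6 = 0.2 and 0.5 + 0.5 × 0.6 = 0.8. The indirect effect is 0 × 0.2 = 0 × 0.8 = 0.

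Rejection rates over 4000 simulated trials, two-sided alpha 0.05:

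| Scenario | T × M interaction test | Joint test of both links (a and b) | Mean estimated indirect effect |
|---|---|---|---|
| A: full mediation | 4.6% | 87.4% | 0.30 |
| B: no mediation, interaction present | 85.4% | 4.5% | about 0 |
| All effects zero | 5.1% | 0.2% | about 0 |

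The interaction test stays at its false-positive rate under full mediation and rejects freely when there is no mediation.

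**Reading 2: mindfulness as a second repeated measure.** Take d = 0 and put both scores on a common scale. The arm difference is a for mindfulness and c + a·b for the outcome. The arm-by-measure interaction therefore tests (c + a·b) − a = c − a(1 − b).

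- Under full mediation (c = 0) this is −a(1 − b), which vanishes as b approaches 1.
- With no mediation and only a direct effect (a = 0) it equals c.

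This compares two arm differences. It does not estimate the product a·b.

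**Timing.** The mediation sentence does not say which mindfulness visit goes with which outcome visit. T1, T2 and T3 are available for both, so T2 mindfulness can be paired with the T3 outcome.

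**A check on the replacement.** Adjusting the T3 model for T2 outcome may look attractive, but it can remove the effect being sought. Suppose arm raises T2 mindfulness by 0.6, mindfulness affects T2 outcome by 0.5, and T2 outcome carries over to T3 by 0.7 (all assumed). The mediated effect at T3 is 0.6 × 0.5 × 0.7 = 0.21. Given T2 outcome, the coefficient of T2 mindfulness is zero, so that model would report no mediation.

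**The case against.** The strongest defence has three parts.

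First, the article defers to a cited guideline, and a journal article is a condensed account. The guideline may call for further steps, such as a test of arm on mindfulness or a required time order. This cannot be checked from the document. The point stands as a limit on what can be claimed, but a citation does not make a person-level score a within-subjects factor, and the stated wording would still need correcting.

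Second, the article uses the word factor loosely: it applies it to age and number of accesses as well. Within-subjects may simply mean measured repeatedly. The fitted model would then also give a main effect of mindfulness, and mindfulness is itself a secondary outcome, so its arm difference is of interest too. An arm-by-mindfulness term can also belong in a mediation model. All this is fair: the ingredients may be there. The text still names only interactions as what will be explored, and the simulation concerns that term alone, not everything the fitted model could show.

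Third, mediation is not among the listed aims, and the remark about processes of change is a sentence in the Discussion. That stands, and it limits the severity.

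A reader might also infer that the plan ignores time order or pairs measurements from the same visit. The document does not support this. It is silent on pairing, and its three assessments allow a lag.

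**Conclusion.** The point holds for the method as stated. A treatment-by-mindfulness interaction answers a moderation question and is not an estimate of the indirect effect, whether mindfulness is read as a predictor or as a second repeated measure. The conclusion follows from the algebra. The rejection rates (4.6% under full mediation, 85.4% with none) illustrate it on assumed path sizes and do not predict this trial's results.

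Two stronger inferences fail. A reader might conclude that the mediation finding would be wrong whatever the result. It could err in either direction, but the interaction test and a proper mediation analysis can also agree. A reader might also think the main results are compromised. They are not: the six primary treatment-by-time tests do not depend on this analysis. It is a secondary correction of lower severity. It assumes that the meditation level means the mindfulness score, and that the guideline, which is not shown, does not replace the stated test.

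**What to change.** Replace the mediation sentence with an exploratory regression-based analysis for each primary outcome, run separately for patients and caregivers as in the primary models:

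- (a) Regress T2 mindfulness on arm, adjusting for baseline mindfulness, baseline outcome and the stratification factor.
- (b) Regress T3 outcome on arm and T2 mindfulness, adjusting for the same baseline variables but not for T2 outcome.
- Report the indirect effect with a bootstrap 95% CI. If an arm-by-mindfulness term is kept, the indirect effect is no longer a single number, so define it explicitly, for example separately at each arm level.
- State the assumption of no unmeasured confounding between mediator and outcome. Note that T2 mindfulness and T2 outcome come from the same visit, so their order is not observed. Add a sensitivity analysis for this assumption.

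The cost is a change of wording and a little more analysis work, using assessments already planned. The downside is reliance on a confounding assumption that cannot be tested, because mindfulness at T2 is not randomised. That is why the analysis should be labelled exploratory.

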### Meditation and control protocols and software development

The first part of the project is dedicated to the adaptation of the meditation protocol to MS requirements and clinical peculiarities, the creation of the software, and a testing phase. To maximize its effectiveness [19], the meditation protocol will consider the potential impact of MS symptoms (e.g., numbness, fatigue, tingling), implementing meaningful changes to be more MS-related than the original mindfulness-based stress reduction protocol, for example, by implementing music meditation experiences and relaxation exercises. The protocol will be implemented using multimedia software, which will provide the learning and the practice of the intervention. It will be a course, provided with audio and video stimulations, with multiple interactions with the trainer. At the same time, an online control intervention will be implemented. This control intervention includes a psycho-education online program about MS, characterized by interviews, practical advice, and exercises [20]. The contact time commitment will be the same for both conditions.

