The Medical Outcomes Study sleep measure will be used to investigate the quality of sleep [27]. This measure is composed of ten items, recording on a Likert scale the frequency of occurrence in the previous 4 weeks of symptoms and difficulties typically affecting sleep and daytime activities of patients with chronic illnesses.

Rates of refusal to join the interventions groups after randomization, as well as drop-out rates, will be assessed. The software used will keep an access log, recording the number and duration of accesses, together with a track of used tasks.

The psychological assessment phase will begin with the baseline evaluation, at month 6, with the beginning of the intervention phase. It will last 15 months (6 months after the end of the recruitment phase, to allow follow-up assessments).

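### Number of software accesses is planned as a moderator alongside sex and age, but it arises after randomisation, so that analysis does not compare randomised groups

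*Protocol article*

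**What the plan says.** The Analysis section of the protocol article states that "moderation effects by sex, age, and number of accesses to the software will be examined by adding the relative between-subjects factors". About these added terms it then says that "the interactions with the treatment effect will be explored according to the same guidelines". Accesses are thus handled exactly as sex and age are. Nothing marks the analysis of accesses as non-randomised, and no adjustment for selection is described.

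The end of the Self-report measures section shows where the count comes from: "The software used will keep an access log, recording the number and duration of accesses, together with a track of used tasks". The same paragraph anticipates non-participation: "Rates of refusal to join the interventions groups after randomization, as well as drop-out rates, will be assessed".

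The two arms use different products. In the section on protocols and software development, the control is described thus: "This control intervention includes a psycho-education online program about MS, characterized by interviews, practical advice, and exercises". It adds: "The contact time commitment will be the same for both conditions". Allocation is equal, with "60 patients + their caregivers for each groups" (Screening, assessments, and randomization).

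**The concern.** A moderator analysis asks whether the treatment effect differs between kinds of participant. It keeps the protection of randomisation only if the kind is fixed before allocation, because each level then contains a randomised comparison. Sex and age meet that condition. Accesses do not: the count is zero for everyone at allocation and is then produced by what the participant does with the assigned programme.

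Frequent users of a meditation course need not resemble frequent users of a psycho-education programme. Someone who refuses after randomisation or drops out will have few or no accesses, so the low-access group partly records non-participation. The contrast between arms within an access level then mixes any treatment effect with differences in who reached that level.

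At stake is a usage-benefit message. The Discussion hopes to learn about how change comes about and envisages wide, free online access. A finding that benefit grows with log-ins would be an attractive result there, and this analysis can produce it when treatment does nothing.

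**Working it through.** The article gives no figure for this analysis, so there is none to reproduce. The check has two parts.

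**1. Timing of each moderator**

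| Variable | When fixed | Can allocation affect it? |
|---|---|---|
| Sex, age | Before randomisation | No |
| Number of accesses | During use of the assigned programme | Possibly |

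This follows from the Analysis and Self-report measures sections and needs no assumption.

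**2. Possible size, with a true treatment effect of zero**

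Inputs from the article: two equal arms; N = 110 (power statement) or 120 (recruitment target). Assumed, because the article gives no values: an unmeasured prognostic trait, such as motivation, correlates g with outcome, and b_M (meditation) or b_C (control) with accesses. Outcome, trait and accesses are on SD scales.

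*(a) Accesses as a continuous term, N = 110.* The expected false interaction is the difference between the two within-arm slopes, g × (b_M − b_C). Its standard error is about √(1/55 + 1/55) = 0.191. With z = g(b_M − b_C)/0.191, the two-sided rejection rate at 0.05 is about Φ(−1.96 + z) + Φ(−1.96 − z).

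| b_M | b_C | g | False interaction | z | Rate, formula | Rate, simulated (4000 trials) |
|---|---|---|---|---|---|---|
| 0.5 | 0.2 | 0.3 | 0.09 | 0.47 | 7.6% | 7.4% |
| 0.5 | 0 | 0.3 | 0.15 | 0.79 | 12.3% | 11.8% |
| 0.6 | 0.2 | 0.5 | 0.20 | 1.05 | 18.2% | 17.8% |
| 0.6 | 0 | 0.5 | 0.30 | 1.57 | 35.0% | 34.5% |

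A repeat simulation of these rows gave 7.8%, 12.7%, 18.7% and 35.5%. With b_M = b_C (0.3, 0.5 or 0.6), the false interaction is zero and the simulated rate was 4.6% to 5.2%. With a gap of 0.1 between arms it was 5.4% to 5.5%.

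*(b) Accesses split at the overall median, N = 120, g = 0.5, equal mean accesses.* The false effect in the high-access group is g(b_M − b_C) × 0.798, where 0.798 is the mean of the upper half of a standard normal. The low-access group has the opposite sign.

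- 0.3 versus 0: 0.5 × 0.3 × 0.798 = 0.12 SD. Simulated −0.11 (low) and +0.12 (high); interaction rejected in 9.6%.
- 0.5 versus 0: 0.5 × 0.5 × 0.798 = 0.20 SD. Simulated −0.21 and +0.19; rejected in 18.6%.

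*(c) Same split, b_M = b_C = 0.5, but mean accesses higher by s SD in meditation.* By symmetry the cut lies s/2 above the control mean and s/2 below the meditation mean. The false effect in each subgroup is g × b × [φ(s/2)/Φ(s/2) − φ(s/2)/(1 − Φ(s/2))].

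- s = 0.5: 0.25 × (0.646 − 0.964) = −0.08 SD. Simulated −0.08 in both subgroups; rejected in 4.8%.
- s = 1: 0.25 × (0.509 − 1.141) = −0.16 SD. Simulated −0.15 in both; rejected in 5.5%.

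A difference in access level alone therefore leaves the interaction test sound but biases the subgroup effects. The test itself is inflated when the relation between accesses and prognosis differs by arm.

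**The case against.** The strongest reply is that little hangs on this analysis. Moderation is introduced as an addition to the main models, it is to be explored, and the article makes no dose-response claim. Contact time is planned to be equal, no access counts by arm are given, and the marked inflation appears only when accesses track prognosis much more strongly in one arm, which nothing in the article establishes.

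Most of this stands as a limit on size. A reader might infer that accesses are known to differ by arm. They are not: this is a reasonable inference from two different programmes, no more. A reader might also take 7% to 35% as the error rate to expect, but it covers only the assumed settings with a clear difference between arms.

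The reply does not remove the point. Equal planned time does not equalise actual use, or who chooses to use each programme. Exploratory status does not turn a post-randomisation count into a baseline characteristic, and the article states this analysis explicitly rather than leaving it open.

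A further tempting reading is that calling age a between-subjects factor means cutting it into categories. The article names no groups or cut-points, and a general linear model can take age as a continuous term, so that reading is unsupported.

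**Conclusion.** The point holds for one analysis. Number of accesses is a post-randomisation variable given the role of a baseline moderator, and neither its interaction with treatment nor the effects within access subgroups has the protection of randomisation. That conclusion rests on the article's text alone.

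The magnitude rests on assumed correlations and ranges from no inflation of the interaction test to a rate of about one in three in the most unequal setting examined. A non-significant interaction is no reassurance about subgroup effects, as case (c) shows.

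It would be wrong to infer that the trial's main conclusions are at risk or that intention-to-treat has been abandoned. The six primary treatment-by-time models, their 0.008 threshold and the moderation by sex and age do not involve the access count.

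**What to change.** In the Analysis section, restrict moderation to variables fixed before randomisation, which means the planned sex and age. Delete number of accesses from that sentence and add one that puts the log to another use: accesses summarised by arm, together with the refusal and drop-out rates already planned. If a relation between use and outcome is still wanted, present it as an exploratory adherence analysis, stated to be non-randomised and open to confounding by motivation and response.

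A complier-average estimate with randomisation as the instrument is not a safe substitute. It requires allocation to act on outcome only through use of meditation, and here allocation also determines whether the participant receives active psycho-education.

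The change costs a few words and needs no new data. The downside is that the trial could not claim that using the software more causes more benefit, a claim that the planned analysis could not support either.
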